#### Control

Participants in the control group will receive only a static webpage with links to external evidence-based materials written for consumers on asthma management available in Australia without the PCHMS features listed previously (ie, myDr.com.au, HealthInSite.gov.au, and asthmaaustralia.org.au), and delayed access to the full interactive version of *Healthy.me* by 12 months.

### Sample Size

A conservative estimate of at least 300 participants with 150 in each arm is needed to detect a 15% point difference in possession rate of a written asthma action plan between the control group (14.4%) and the intervention group (29.4%). This estimate is calculated at 5% level of significance, 80% power (2-sided test), with an anticipated participant dropout rate approximately 25%.

The effect size estimate is based on previous studies using *Healthy.me* assessing the efficacy of Internet-based interventions on the uptake of preventative health actions [23], and on studies with interventions promoting the use of personal asthma action plans [13]. The base rate is the percentage of adults (ie, 15 years and over) with current asthma in Australia and possessing a written asthma action plan, reported in the Australia Centre for Asthma Monitoring analysis of the Australian Bureau of Statistics National Health Survey 2007-2008, and cited in the Australia Centre for Asthma Monitoring 2011 report [2].

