**Methods:**

The PCHMS integrates an untethered personal health record with consumer care pathways and social forums. After eligibility assessment, a sample of 300 adult patients with moderate persistent asthma will be randomly assigned to one of these arms. After 12 months of using either Healthy.me or information websites (usual care arm), a post-study assessment will be conducted.

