## Introduction

### Background

Around 300 million people worldwide currently suffer from asthma [1]. The mortality caused by asthma is significant since a global estimation attributes to this disease about 1 in every 250 deaths [1]. Living with asthma is also difficult. People with asthma report worse health and quality of life than those without asthma [2,3].

Solutions have been developed to help people with asthma cope with their condition [4]. One of the key elements to optimal asthma management is to achieve good control of the disease. To achieve that, patients’ knowledge in recognizing asthma symptoms, identifying risk factors, using medication, and managing asthma exacerbations is important. Further, the relationship between patients with asthma and healthcare providers is crucial to develop an efficient asthma self-management plan [5].

One of the most useful tools in facilitating effective asthma self-management is the use of an individualized written asthma action plan, which describes different tailored steps of actions for the patient to follow according to their asthma severity. Written asthma action plans are claimed to be one of the most effective means for asthma self-management in several systematic reviews [6-8]. A Cochrane review by Gibson and colleagues concludes that use of a written asthma action plan, combined with regular visits to the doctor and education about asthma, leads to fewer visits to the emergency department, less hospital admissions, better lung function, and improvement on symptoms [6]. Online social networks and personal health management systems represent an innovative intervention to help patients engage with clinicians, health services, and self-management [9]. Despite strong evidence for the efficacy of written asthma action plans, they are widely under-used. Even after over 20 years of recommendation, only about one in 5 people with asthma have a written asthma action plan [10].

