#### Recruitment Strategy

The recruitment of participants will be made possible with the assistance of Asthma Foundation Australia, the National Asthma Council Australia, and other consumer groups which have an online presence, to advertise our study using their existing participant engagement methods (ie, electronic newsletters and website). Because the study requires participants who are familiar with the use of the Internet, special emphasis will be given to Internet-based recruitment. Calls for research participants will be made on Google, Facebook, Twitter, and other online/social media on a regular basis, as well as on an online notice board (Gumtree Australia). It will also be possible that some participants will be recruited by others participants (snowballing sampling) via sharing in social networks, and thanks to the “invite a friend” feature they will be able to use on *Healthy.me* website.

Interested participants will be directed to a website with detailed information about the study. All consenting participants (control and intervention) will then be directed to a secure website to complete an eligibility screening survey.

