### Study Procedure

Table 3 below summarizes participant procedures in the study. The duration of the study is expected to be 12 months.

Email will be the primary channel to communicate with participants for study information and reminders about survey completion. From the time participants are recruited until study completion, all participants (control and intervention) will receive an email each month to complete a 5-minute survey about their health in the past month. At study completion, all participants will receive an email asking them to complete a post-study survey. In order to ensure the completeness of data collection, there will be 2 follow-up emails sent 5 days apart from each other to remind those who have not completed each survey.

**Table 2 table2:** Surveys used in the study.

Survey	Purpose
Screening survey	Eliciting participants’ eligibility criteria.
Pre-trial survey	To obtain participants’ demographics and experiences of asthma management at study enrolment.
Monthly follow-up questions	To obtain participants’ self-reported symptoms of asthma (ie, asthma control and exacerbation), impact on work and study due to asthma symptoms, and competing demands and health throughout the study.
Post-trial survey (12 months after the beginning of the study)	To obtain participants’ state of asthma control and asthma management. For those who receive the PCHMS version of *Healthy.me*, their perceived usefulness of *Healthy.me* will also be assessed.

**Table 3 table3:** Stages of study procedure.

Stage of study	Procedure

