## Discussion

### Limitations

There are several potential limitations in this study. Firstly, the number of participants meeting inclusion criteria at study completion might be low because the study will focus recruitment only in Australia. The other inclusion criteria such as age, Internet access, and English speaking skills, might be also restrictive for recruiting participant in the targeted population.

Secondly, there is a possible high attrition rates*.* The study’s outcomes will rely on data from participants’ self-reports. Due to the long duration of the study, over 12 months, it is possible to observe a high rate of attrition from participants and thus, a significant loss of data. To limit this, all participants will be actively requested to complete questionnaires by receiving monthly reminders via emails. Furthermore, the questionnaires used on a monthly-basis will be easy and convenient complete (short questionnaires with an online completion using multiple-choice questions).

Thirdly, there may not be representative of consumers with asthma. The study may be more appealing to younger participants who are interested or literate in computers, the Internet, or asthma self-management topics. These participants may be more enthusiastic about health and the Internet than the general asthma population.

Fourthly, as this is a pragmatic trial of a multifaceted intervention in a complex environment, it is possible that baseline variables associated with participants might also influence the outcome. For example, having a prior history of obtaining a written asthma action plan may predict future planned visits to GP, independent of any additional intervention. We will identify potential baseline variables that might influence outcomes, including age and smoking status, and test for unequal variance in the distribution of these variables in the intervention and control populations.

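### The 300-participant estimate is called conservative, but at the plan's own rates and dropout it gives about 78% power, and the 14.4% base rate is only a community proxy for the trial's endpoint

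*Protocol article*

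**What the plan says.** All references are to the protocol article. Sample Size gives the estimate: "A conservative estimate of at least 300 participants with 150 in each arm is needed to detect a 15% point difference in possession rate". The assumed rates are 14.4% in controls and 29.4% in the intervention arm, with a two-sided 5% test, 80% power and dropout of about 25%. The same section gives the source of the control rate: "The base rate is the percentage of adults (ie, 15 years and over) with current asthma in Australia and possessing a written asthma action plan". That source is the 2007-2008 National Health Survey.

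The text of Outcome Measures defines the primary outcome as the number of participants who obtain or update a plan with a GP within the 12 months, and Primary Analysis compares that proportion.

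On who the controls are, Recruitment Strategy describes advertising "with the assistance of Asthma Foundation Australia, the National Asthma Council Australia, and other consumer groups which have an online presence", and also through search engines, social media, an online notice board and snowballing. Intervention and Control describes all participants as volunteers. Under Control: "Participants in the control group will receive only a static webpage with links to external evidence-based materials written for consumers on asthma management". Limitations says of the sample: "These participants may be more enthusiastic about health and the Internet than the general asthma population".

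**The concern.** Two features of the sizing do not support the word conservative. First, the allowance for dropout seems too small to preserve 80% power at the stated rates. Second, the control rate comes from a different population and a different quantity: how many people in the community hold a plan, rather than how many volunteers obtain or update one in a year. When the absolute difference is fixed, a lower control rate (anywhere below about 42%) means less variance and a smaller required sample. A low base rate is therefore the favourable choice for sample size, not the cautious one.

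At stake is how a null result would be read. If power is nearer 65-70% than 80%, a true 15-point benefit would be missed about a third of the time. A reader relying on the stated 80% would take the result as stronger evidence against Healthy.me than it is.

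**Working it through.** **Inputs.** From Sample Size: control rate p_C = 0.144, intervention rate p_I = 0.294, difference d = 0.15, two-sided 5% (z = 1.960), 80% power (z = 0.842), loss 25%, 150 per arm. From Study Design: 1:1 allocation. The other control rates below are assumed.

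**1. Reproduce the plan's figure.** Let p̄ be the mean of the two rates and q = 1 − p.

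n per arm = [1.960·√(2p̄q̄) + 0.842·√(p_C q_C + p_I q_I)]² / d²

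- p̄ = 0.219, so √(2 × 0.219 × 0.781) = 0.5849
- √(0.144 × 0.856 + 0.294 × 0.706) = 0.5752
- n = (1.1463 + 0.4841)² / 0.0225 = 118.1, so 119 per arm

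Multiplying by 1.25 gives 119 × 1.25 = 148.75, so 149 per arm, or 298, which matches the stated 300. Dividing by 1 − 0.25 gives 119 / 0.75 = 158.7, so 159 per arm, or 318. The stated figure therefore matches multiplication by 1.25, which does not leave 119 after a 25% loss: 149 × 0.75 = 111.75.

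**2. Power at the plan's own rates.** 150 × 0.75 = 112.5; take 112 per arm.

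Power = Φ{[d√n − 1.960·√(2p̄q̄)] / √(p_C q_C + p_I q_I)}

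d√n = 0.15 × √112 = 1.5875, so (1.5875 − 1.1463) / 0.5752 = 0.767 and power is 77.8%. With 113 per arm it is 78.2%. Exact enumeration of the uncorrected chi-square test at 112 gives 78.3%.

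**3. Same formula, n = 112, 15 points fixed, other control rates.**

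| Control | Intervention | 1.960·√(2p̄q̄) | √(p_C q_C + p_I q_I) | z | Power |
|---|---|---|---|---|---|
| 10% | 25% | 1.0532 | 0.5268 | 1.014 | 84.5% |
| 12% | 27% | 1.0982 | 0.5502 | 0.889 | 81.3% |
| 14.4% | 29.4% | 1.1463 | 0.5752 | 0.767 | 77.8% |
| 20% | 35% | 1.2377 | 0.6225 | 0.562 | 71.3% |
| 25% | 40% | 1.2982 | 0.6538 | 0.442 | 67.1% |
| 30% | 45% | 1.3419 | 0.6764 | 0.363 | 64.2% |

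At 112.5 per arm, power falls through 80% at a control rate of about 13.0% and does not return to 80% until about 72%.

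**4. Separate the two causes.** The shortfall at 14.4% (80 − 77.8 = 2.2 points) comes from the dropout inflation alone. A higher control rate would cost a further 77.8 − 71.3 = 6.5 points at 20%, 10.7 at 25% and 13.6 at 30%.

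**5. Check whether LOCF restores the power.** Primary Analysis carries the last observation forward, so 150 per arm could be analysed. If the 25% lost count as no event, the rates become 0.75 × 0.144 = 0.108 and 0.75 × 0.294 = 0.2205, and power is 75.1%. If the lost keep a 14.4% baseline rate in both arms, the contrast is 0.144 versus 0.144 + 0.75 × 0.15 = 0.2565, and power is 68.4%. Neither reaches 80%.

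**The case against.** The best defence is that 14.4% is the only figure in the article that roughly matches the trial's adult population. That stands. Background also gives 21.3%, and says that "only about one in 5 people with asthma have a written asthma action plan", but the first is an all-age figure and the second covers people with asthma generally. A reader might infer that the authors picked the lowest of several equal candidates, or that the article's own alternatives cost 6.5 to 7.7 points of power. The article does not support that, since 14.4% is the age-matched choice. The 20% to 30% rates above are assumptions only.

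A reader might also infer that the control rate must exceed 14.4%. Self-selection and the information page make this plausible, but Limitations says only that participants may be more enthusiastic. The yearly obtain-or-update rate could also be lower than the prevalence of holding a plan, which would raise power. Table 1 words the primary outcome as having a plan, which is closer to the base rate, but the section text and Primary Analysis use obtaining or updating. An effect of the monthly survey emails on plan uptake is speculation, because Table 1 lists plan possession only at baseline and completion.

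It is fair, too, that the result depends on the loss and the effect scale. With all 150 per arm evaluable, power is 88.5% at 14.4% and stays at or above 80% up to about 24%. With a constant odds ratio of 2.48, power would rise to 86% at a 20% control rate. But Sample Size itself anticipates 25% loss and fixes an absolute difference.

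Finally, an article commonly leaves a full sensitivity table to other documents. The point here is not a missing table: the stated 80% and the word conservative do not follow from the stated inputs.

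**Conclusion.** The point holds in limited form. On the plan's own inputs, power is about 78%, not 80%, and there is no reserve that would justify calling 300 conservative. The 14.4% is a proxy for the control rate on the actual endpoint, and the error could run either way: about 85% power at 10%, 71% at 20%, 67% at 25% and 64% at 30%. These figures assume a fixed 15-point difference, 112 evaluable per arm and a two-sided 5% test without continuity correction.

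Three stronger readings are not supported:

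- Raising controls to 21.3% while leaving the intervention arm at 29.4% gives about 29% power. That moves one arm only, although self-selection and the surveys apply to both.
- Plan possession in the pre-study survey might seem to show which power figure applies. It does not: someone holding an old plan who never updates it counts at baseline but not in a 12-month obtain-or-update outcome.
- The abstract's phrase, "After 12 months of using either Healthy.me or information websites (usual care arm), a post-study assessment will be conducted", might be read as hiding the true comparator. The article openly describes that comparator as static websites, so the label is a matter of preference.

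**What to change.** In Sample Size:

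- Delete the word conservative.
- State that 14.4% is a community possession rate in people aged 15 and over, used as a proxy for the 12-month obtain-or-update rate in the recruited volunteers.
- Restate power for a 15-point difference at 300 enrolled with 25% loss as about 78% at 14.4%, with a range from about 85% at a control rate of 10% to 64% at 30%. Label the rates other than 14.4% as assumptions.

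This changes wording only and needs no extra participants or data. The cost is a less favourable stated power.

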## Methods

### Study Design

A randomized controlled trial with a 2-group parallel design (with intervention allocation ratio 1:1) will be used to evaluate the efficacy of the Web-based PCHMS *Healthy.me*, reported in accordance to the 2010 CONSORT statements [27](ACTRN12612000716864). The PCHMS is not part of usual care but aims to improve usual care as measured by compliance to evidence-based guidelines.

Participants randomized to the *intervention* group will have immediate access to an interactive version of *Healthy.me* with full PCHMS features as described later, from the date they are recruited.Participants randomized to the *control* group will receive access to a static webpage, without PCHMS features or any interactive component. This webpage will offer links to Australian information websites about asthma.

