#### Primary Analysis

Differences in proportions of participants visiting their GP to obtain/update their written asthma action plan during the study will be compared between control and PCHMS groups. All intervention recipients who had the opportunity to use the PCHMS but did not do so will be included in the primary analysis (intention-to-treat principle with Last Observation Carried Forward (LOCF) imputation procedure for missing values [35,36]). Differences in participant proportions between control and PCHMS groups will be analyzed using χ^2^test or Student’s *t*-test. Proportions will be reported with 95% confidence intervals. Adjustments for baseline characteristics and possible confounders, such as age and other demographics [2,3], smoking status [3], and asthma severity [2], will be made through the use of sequential logistic regression [37]. All baseline characteristics, and factors that may affect the written asthma action plan possession rate collected at post study (eg, past possession of an asthma action plan) will be entered at step 1 of the regression; and group allocation (PCHMS vs. control) will be entered at step 2.

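### Under its own inputs, 300 randomised with 25% dropout gives about 78–79% power, so the sample size is slightly short of 80% and is not a conservative minimum

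*Protocol article*

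**What the plan says.** The Sample Size section of the protocol article gives the size as "A conservative estimate of at least 300 participants with 150 in each arm is needed to detect a 15% point difference". The difference is in the "possession rate of a written asthma action plan between the control group (14.4%) and the intervention group (29.4"%). The error rates are given as "This estimate is calculated at 5% level of significance, 80% power (2-sided test"), "with an anticipated participant dropout rate approximately 25"%. The section does not give the formula, the evaluable number per arm or the way dropout was applied.

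The Study Design section sets a "2-group parallel design (with intervention allocation ratio 1:1"). The Primary Analysis section says: "Differences in participant proportions between control and PCHMS groups will be analyzed using χ^2^test", with Student's t-test named as an alternative. It handles missing data by the "intention-to-treat principle with Last Observation Carried Forward (LOCF) imputation procedure for missing values". Table 1 has the primary outcome collected by survey at baseline and at completion only.

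**The concern.** A sample size described as conservative should be at least as large as its own assumptions require. Here the stated size appears to fall a little below that, so the stated power is slightly overstated at the stated dropout.

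There is also a mismatch between two sections. Inflating for dropout implies that dropouts leave the analysis, whereas the primary analysis retains them by imputation. The power quoted in one section is therefore not clearly the power of the analysis described in the other. A null result would be read against the 80%, so the figure should match the planned analysis or carry its conditions.

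**Working it through.** **Inputs.** From Sample Size: p1 = 0.144, p2 = 0.294, difference 0.15, two-sided 5% (z = 1.960), 80% power (z = 0.842), dropout 0.25, 150 per arm. From Study Design: 1:1 allocation. From Primary Analysis: χ² test, with no continuity correction specified.

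**Evaluable number per arm.** The mean rate is 0.219. The null variance term is 2 × 0.219 × 0.781 = 0.3421 (root 0.5849). The alternative variance term is 0.144 × 0.856 + 0.294 × 0.706 = 0.3308 (root 0.5752).

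- Pooled: n = (1.960 × 0.5849 + 0.842 × 0.5752)² / 0.15² = 118.1, so 119.
- Simple pooled (null variance throughout): n = (1.960 + 0.842)² × 0.3421 / 0.0225 = 119.3, so 120.
- Unpooled: n = (1.960 + 0.842)² × 0.3308 / 0.0225 = 115.4, so 116.
- Arcsine: 116.1, so 117.

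**Reproducing the stated 150 per arm.** Multiplying by 1.25 gives 119 × 1.25 = 148.8, so 149 (298 in total). With the simple pooled formula it gives 120 × 1.25 = 150 exactly (300 in total). The stated figure is consistent with this route.

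**Dividing by the retained fraction, 0.75.**

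| Formula | Evaluable per arm | Randomised per arm | Total |
|---|---|---|---|
| Unpooled, rounded only at the end | 115.4 | 154 | 308 |
| Unpooled | 116 | 155 | 310 |
| Arcsine | 117 | 156 | 312 |
| Pooled | 119 | 159 | 318 |
| Simple pooled | 120 | 160 | 320 |

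**Power with 300 randomised and 25% dropout.** 150 × 0.75 = 112.5, so 112 or 113 per arm. The pooled formula is power = Φ[(0.15 × √n − 1.960 × 0.5849) / 0.5752]. At n = 112 this is Φ[(1.587 − 1.146) / 0.5752] = Φ(0.767) = 77.8%.

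| Method | n = 112 | n = 113 |
|---|---|---|
| Pooled | 77.8% | 78.2% |
| Exact enumeration of the χ² test | 78.3% | 78.8% |
| Arcsine | 78.6% | 78.9% |
| Unpooled | 78.8% | 79.2% |

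None of these reaches 80%.

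**Dropout at which 150 per arm still holds 80%.** Pooled: 1 − 119/150 = 20.7%, or 1 − 118.1/150 = 21.2% without rounding up. Unpooled: 1 − 115.4/150 = 23.1%.

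**Power if all 300 are analysed, as the LOCF plan implies.** The article does not say whether 14.4% and 29.4% describe completers or everyone randomised, nor what baseline possession will be in the sample. The following are therefore assumptions, each with 150 per arm and the pooled formula.

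- *Completer rates; dropouts in both arms hold a plan at 14.4%.* Intervention: 0.75 × 29.4 + 0.25 × 14.4 = 25.65%. Control: 14.4%. Power 68.4%.
- *Completer rates; all dropouts count as having no new or updated plan.* Intervention: 0.75 × 29.4 = 22.05%. Control: 0.75 × 14.4 = 10.8%. Power 75.1%.
- *The stated rates apply to all 300 randomised.* 14.4% versus 29.4%. Power 88.5%.

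In the first two cases the difference shrinks from 15 to 11.25 points; in the third it does not.

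**The case against.** The strongest reply is that the gap is too small to matter. On a completer basis it is 1–2 points, the dropout is only approximate, and the unpooled formula needs 308, so 300 falls 8 short (8/308 = 2.6%). This stands as a limit on the size of the point. It does not reverse the direction: every two-sided formula tried gives a total above 300 and power below 80%.

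Three stronger readings are tempting and not supported.

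- *The planners multiplied by 1.25 when they should have divided by 0.75.* The numbers fit, but the article shows neither the formula nor the inflation step. The shortfall does not depend on how 300 was reached.
- *The design has only 68–75% power.* Those figures require 14.4% and 29.4% to be completer rates and dropouts to carry no intervention effect. The article states neither, and the control rate is a population survey figure. If the rates describe everyone randomised, power is 88.5%.
- *Power is lower still with a continuity correction.* The Primary Analysis section specifies no such correction, so this is not the planned test.

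It can also be said that conservative may refer to the assumed effect, and that the size is given only as a floor. The sentence, however, attaches the word to the participant number, and a floor below the number required is not a conservative one.

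**Conclusion.** The point holds as a minor one. On the stated rates, two-sided 5% level and 80% power, with dropouts leaving the analysis, 25% dropout calls for about 308–320 randomised. With 300, power is about 78–79%. Calling the stated power simply wrong would be too strong; it is slightly overstated at 25% dropout and attained up to about 21% (pooled formula).

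The more useful observation is that the Sample Size and Primary Analysis sections imply different analysis sets. Under LOCF the power could be 68%, 75% or 88.5%, depending on assumptions that the article leaves open. None of the three can be presented as the power of the design without its assumption.

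**What to change.** In Sample Size, delete the word conservative, name the formula, and replace the claim with: *About 119 evaluable participants per arm are needed; 300 randomised give 80% power if dropout is at most about 21%, and about 78% at 25% dropout.*

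Then say whether dropouts leave the primary analysis or are imputed. If LOCF is kept, say whether 14.4% and 29.4% refer to completers or to all randomised, and give the matching power with its assumption: 68% if dropouts in both arms hold a plan at 14.4%, 75% if all dropouts count as having no new or updated plan, and 88.5% if the stated rates apply to all 300.

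The cost is a few restated sentences and a slightly less favourable power figure. No extra enrolment is needed.
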